# Standing Practice In Rehabilitation Early after Stroke (SPIRES): a functional standing frame programme (prolonged standing and repeated sit to stand) to improve function and quality of life and reduce neuromuscular impairment in people with severe sub-acute stroke—a protocol for a feasibility randomised controlled trial

**DOI:** 10.1186/s40814-018-0254-z

**Published:** 2018-03-23

**Keywords:** Stroke, Supported standing, Neuromuscular impairment, Physiotherapy, Function, Feasibility randomised controlled trial, Early mobilisation

## Abstract

**Background:**

The most common physical deficit caused by a stroke is muscle weakness which limits a person’s mobility. Mobility encompasses activities necessary for daily functioning: getting in and out bed, on/off toilet, sitting, standing and walking. These activities are significantly affected in people with severe stroke who typically spend most of their time in bed or a chair and are immobile. Immobility is primarily caused by neurological damage but exacerbated by secondary changes in musculoskeletal and cardiorespiratory systems. These secondary changes can theoretically be prevented or minimised by early mobilisation, in this case standing up early post-stroke.

Standing up early post-stroke has been identified as an important priority for people who have suffered a severe stroke. However, trials of prolonged passive standing have not demonstrated any functional improvements. Conversely, task-specific training such as repeated sit-to-stand has demonstrated positive functional benefits. This feasibility trial combines prolonged standing and task-specific strength training with the aim of determining whether this novel combination of physiotherapy interventions is feasible for people with severe stroke as well as the overall feasibility of delivering the trial.

**Methods/design:**

This is a pragmatic multi-centre parallel single-blinded two-armed feasibility randomised controlled trial. Fifty people with a diagnosis of severe stroke will be randomly allocated to either the functional standing frame programme or usual physiotherapy. All patient participants will be assessed at baseline and followed up at 3 weeks, then 3, 6 and 12 months post-randomisation. Trial objectives are to determine the feasibility according to the following indicators:: (i) *Process*: recruitment and retention rate, ability to consent, eligibility criteria, willingness/ability of physiotherapists to recruit, willingness of patients to be randomised, and acceptability of the intervention; (ii) *Resource*: burden and potential costs; (iii) *Management*: treatment fidelity, participant adherence, acceptability and completeness of outcome measures, impact and management or orthostatic hypotension; and (iv) *Safety*: number and nature of adverse and serious adverse events.

**Discussion:**

The functional standing frame programme addresses a key concern for people who have suffered a severe stroke. However, several uncertainties exist which need to be understood prior to progressing to a full-scale trial, including acceptability and tolerance of the functional standing frame programme intervention and practicality of the trial procedures. This feasibility trial will provide important insights to resolve these uncertainties.

**Trial registration:**

International Standard Randomised Controlled Trial Number ISRCTN15412695. Registration on 19 December 2016.

**Electronic supplementary material:**

The online version of this article (10.1186/s40814-018-0254-z) contains supplementary material, which is available to authorized users.

## Background

Stroke is a sudden and devastating illness affecting over 100,000 people per annum in the United Kingdom (UK) [53]. Current government and clinical guidelines recommend that following diagnosis of a stroke, people are admitted to an Acute Stroke Unit to receive stroke specialist multi-disciplinary care. This reduces mortality and improves functional outcomes [40] compared to standard non-specialist care. The UK stroke pathway [44] and National Clinical Guidelines [34] advocate that people with mild or moderate strokes (i.e. modified Rankin Scale (mRS) 1–3; able to transfer independently or with the help of one person with/without equipment) are discharged from the Acute Stroke Unit to the Early Supported Discharge service, which provides specialist stroke rehabilitation in a home-based setting. People with severe strokes (mRS 4–5; requiring assistance of two people with/without equipment) are transferred from the Acute Stroke Unit to a specialist Stroke Rehabilitation Unit for early sub-acute rehabilitation usually within 7 days. The early sub-acute phase spans from 7 days to 3 months [6]), with average time from stroke onset to admission on Stroke Rehabilitation Unit 6 days (1 to 37 days) [13]. Some Early Supported Discharge services in the UK admit people with a mRS of 4, but this is not the standard care nationally.

The implementation of Early Supported Discharge has caused a change in patient caseload nationally for Stroke Rehabilitation Units [54] resulting in the majority of people admitted to Stroke Rehabilitation Units having complex needs and severe deficits. This change in caseload necessitates the design and evaluation of interventions for patients in Stroke Rehabilitation Units that target people with more severe deficits. The most common physical deficit caused by stroke is motor impairment, seen in approximately 80% of people [70]. It is the single most disabling factor in terms of limiting a person’s mobility, their ability to participate in activities of daily living (ADL) and to live independently [67]. Mobility encompasses a wide range of activities necessary for daily functioning: moving in bed, getting in/out of bed, on/off toilet, sitting out of bed, standing and walking [34]. These activities are particularly affected in the 15.5% of people with severe stroke [54] who require the assistance of two people to undertake ADL, may need equipment to aid transfers and are unable to sit unsupported, stand or walk [27]. They typically spend much of their time in bed and are dependent on a wheelchair/specialist seating when they sit out of bed [57].

Although immobility post-stroke is primarily caused by neurological damage, it can be exacerbated by other factors such as muscle wasting [56], reduced muscle length, increased muscle stiffness [47], joint contracture [26] and orthostatic hypotension. Orthostatic Hypotension (OH) is a sudden drop in blood pressure when moving from lying to standing, leading to symptoms of feeling faint, generalised weakness, cognitive slowing, and gradual or sudden loss of consciousness [38] and can, therefore, limit standing time. It can affect over 50% of people post-stroke [37] and should be addressed using non-pharmacological or pharmacological interventions, or a combination of the two [49, 64]. Secondary changes in the musculoskeletal and cardiorespiratory systems can theoretically be prevented or minimised by early mobilisation [65] especially standing [46]; prevention of these secondary changes underpins the rationale for the current trial.

Several randomised controlled trials (RCTs) have reported mixed outcomes of early mobilisation post-stroke. Less favourable outcomes occurred when early mobilisation was instigated *very* early (within the first 24 h post-stroke) [62] compared to a reduction in complications when instigated early (≥ 24 h post-stroke) [17]. Early mobilisation is associated with increased independence in ADL and a faster return to walking [15]. However, these trials all had different primary end-points (Functional Independence Measure; Modified Rankin; incidence of severe complications during hospitalisation) which makes direct comparison of effectiveness of early mobilisation interventions difficult. Whilst early mobilisation is deemed to be safe [5, 15, 17, 62], uncertainties have been identified with regard to dose and frequency. The AVERT Trial Collaborative Group suggest that shorter, more frequent mobilisation is preferable, and the latest Royal College of Physicians Guidelines have incorporated this, recommending patients “accumulate” at least 45 min daily. However, the main limitation of these studies is that they specify neither the time spent mobilising nor the intensity, content and frequency of therapy. Therefore, it is possible in previous work that, other than hoists, no specialised equipment was used to promote recovery for people with severe stroke, and active sitting constituted early mobilisation with no opportunity to stand. This is aligned with current clinical practice in Cornwall and Devon (where this research is being led) where standing is not routinely implemented as part of sub-acute inpatient rehabilitation for people who have suffered a severe stroke.

A motorised standing frame can safely assist people with severe stroke into a supported standing posture. Suggested benefits of supported standing include stretching contracted muscles, decreasing spasticity, strengthening muscles, improving bladder and bowel function, relieving pressure areas and reducing OH [2, 19, 31, 35, 45, 69]. Evidence from people with spinal cord injury, multiple sclerosis, stroke and traumatic brain injury [2, 46, 60] indicates that the aforementioned benefits can be observed with 30 min of regular standing. However, a systematic review highlighted variation in duration (20 to 60 min) and frequency from three times per week (median 5 days per week), with dose dependent on length of inpatient say and participant recovery [46].

In preparation for this feasibility trial, discussions with people who had suffered a stroke and their relatives identified that standing up early after a stroke was important, relevant and meaningful for them and this formed the basis of the research question and subsequent trial design/development. Opportunities to stand for people who have suffered a severe stroke are limited due to significant disability; thus, they are reliant on physical assistance from mechanical equipment such as a standing frame.

Standing frames are not routinely used in sub-acute inpatient stroke rehabilitation as part of a postural management programme and never issued on discharge from Stroke Rehabilitation Units. A systematic review [46] identified a paucity of robust evidence for the use of standing frames in people with stroke. A previous RCT found no difference in functional outcomes in people with a sub-acute severe stroke who did or did not use standing frames for 14 consecutive sessions [1]. The lack of functional improvement may be due to the duration and intensity of treatment, as well as the sensitivity of the outcome measures used (Rivermead Mobility Index and Barthel Index). Additionally, participants undertook prolonged passive standing only and the addition of task-specific training may have improved functional outcomes. Task-specific training is based on the fundamental principle that repeated practice of functionally relevant tasks is the best way to learn [3, 23]. Tasks such as sit-to-stand have been shown to produce functional benefits post-stroke, and patients who receive task-specific training are more likely to improve their function and sustain these improvements than patients receiving usual care [23, 63]. The combination of prolonged standing and task-specific strength training underpins the rationale for the functional standing frame programme used in this feasibility trial.

The functional standing frame intervention combines two physiotherapy interventions that have separately been evaluated and reported in the literature: prolonged standing and task-specific strength training. Currently, it is not known whether this novel combination of physiotherapy for people with severe stroke is effective in everyday clinical practice, and the United Kingdom Medical Research Council provides guidance on how complex interventions can be developed and evaluated [42]. A key component of the evaluation of the complex intervention is the acceptability among people with severe stroke. Currently, it is not known whether the functional standing frame programme would be tolerated or acceptable for people with severe stroke, at this early stage of their rehabilitation continuum. The Medical Research Council guidance explicitly recommends an early phase of assessing feasibility prior to a full definitive main trial [43] and recognises the value of using both quantitative and qualitative methods concurrently. The use of qualitative research within feasibility RCTs is becoming increasingly common [48]. This feasibility randomised controlled trial facilitates the evaluation of acceptability, compliance and delivery of the intervention; trial practices, processes and design; and recruitment and refusal and retention rates. This links to the trial objectives and will inform the conduct and design of the anticipated definitive main trial to facilitate successful, effective and confident delivery.

Qualitative research will be embedded in this feasibility trial and used in tandem with quantitative methods to provide insights into the intervention and trial processes.

## Aims

The *primary aim* of this trial is to establish whether a RCT of a functional standing frame programme in people with severe stroke in an inpatient sub-acute stroke rehabilitation setting is feasible.

The *secondary aim* is to explore the experience of this functional standing frame programme on the individual’s daily life, as well as the experience of being recruited and randomised to the trial, from the perspective of both the person with stroke and their relative/carer, using qualitative methods.

## Objectives

Trial-specific objectives are to evaluate the feasibility according to the following indicators:

### Process

#### Recruitment rate

The recruitment rate will be defined as the number of participants recruited per month. This information was recorded in the study log at each site.

#### Retention rate

The retention rate will be calculated by dividing the number of participants, who completed data collection at T2 (post-intervention), T3 (3-month follow-up), T4 (6-month follow-up) and T5 (12-month follow-up) by the number of participants who completed data collection at T1.

#### Ability to consent

The ability of patient participants to consent will be measured by the number of participants who provided informed consent and the number of consultee declarations [16]. Additionally, incidence of cognitive and communication impairments will be measured from the Screening and Post-Screening and Assessor Case Report Forms.

#### Consent rate

The consent rate will be calculated by dividing the number of individuals who met inclusion criteria, by the number who consented to participate in the trial. Reasons why eligible individuals are not interested in participating will be recorded by the PI/recruiting therapist in the approach/screening log.

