### Sample size

As a feasibility trial, a formal sample size calculation based on considerations of power is not appropriate; this trial is not statistically powered to detect between-group clinically meaningful differences in a primary outcome. One of the objectives of this trial is to provide robust estimates of the likely rates of recruitment and follow-up, as well as provide estimates of the variability of the proposed primary and secondary outcomes to inform sample size calculations for the planned definitive trial. There is no consensus on the recommended number of participants required for a feasibility trial, with published “rules of thumb” ranging from 20 to 70 or more participants, when the planned primary outcome is of a continuous nature. A recent paper recommended a feasibility trial sample size should recruit 25 participants per allocated group, if the planned definitive trial will have a two-arm parallel group design, with 90% power and two-sided 5% significance level, to detect a “small” standardised effect size [71]. Therefore, this feasibility trial aims to recruit 50 participants in total.

A target sample size of 50 patient participants will allow the follow-up rate to be estimated to within ± 15%. The follow-up rate at 12 months is estimated to be 70%, which would provide follow-up outcome data on a minimum of 35 participants across both allocated groups and three sites.

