**Table Taba:** 

Feasibility indicator	Outcome measures	Data collection method
Process		
Recruitment rate	% of participants recruited/time	Case Report Forms
Retention rate	% of participants completed T1, T2, T3, T4, T5	Case Report Forms & Withdrawal Forms
Ability to consent	% of participants consenting	Screening/Approach Logs
Consent rate	% of consultee declarations	Case Report Forms
Eligibility criteria	% of admissions screened & eligible	Screening/Approach Log, Recruitment rate, Interview & Focus Group
Willingness of physiotherapists to recruit	% of admissions screened & approached	Recruitment rate, Interview & Focus Group
Willingness of patients to be randomised	% of participants who refuse to enrol in the trial	Recruitment Rate, Interviews & Focus Group
Acceptability of the intervention	% of withdrawals	Case Report Forms & Interview
Determining usual physiotherapy	Frequency specific physiotherapy interventions are implemented	Case Report Forms
Resources		
Burden	% of participants refusing physiotherapy sessions and follow-up assessments	Case Report Forms & Interviews & focus group
Cost effectiveness	*n* = duration (minutes) of functional standing frame programme session	Case Report Forms & Interviews
Management		
Fidelity	Observe intervention and control group sessions	Fidelity Checklists
Participant adherence	*n* = sessions per week	Case Report Forms
	*n* = minutes in standing	Case Report Forms & interview
	*n* = sit to stand repetitions	Case Report Forms & interview
	*n* = Yes; *n* = No for enjoyment	Case Report Forms & interview
	Score out of 10 for effort	Case Report Forms & interview
	Score out of 10 for fatigue	Case Report Forms & interview
Orthostatic hypotension protocol	% incidence of orthostatic hypotension	Case Report Forms
	% of incomplete sessions due to orthostatic hypotension (OH)	Case Report Forms
Safety		
Intervention	*n* = AE & SAE	Adverse Event and Serious
Data collection	*n* = AE & SAE	Adverse Event Forms

T1: baseline; T2: post-intervention period; T3: 3 months; T4: 6 months; T5: 12 monthsB)Clinical outcome measures

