### Determining progression to the full trial

Progression to a full trial application will occur if minimum success criteria are achieved in key feasibility aims and objectives, and/or if solutions can be identified to overcome any issues. These criteria will be finalised in discussion with the Trial Steering Committee, but are likely to include a minimum of:70% recruitment of the intended 50 patient participants within the 13-month recruitment window80% of consented patient participants randomised to the intervention group engaging with and adhering to a minimum of five session per week during the three-week SPIRES intervention80% completion rate of outcome measures (including follow-up)

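### The consent rate formula is inverted (those meeting criteria divided by those consenting), and the outcome table as printed gives the indicator a different measure

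*Protocol article*

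**What the plan says.** Consent rate is one of the process indicators listed in the protocol article under Objectives. Its subsection says that it is obtained by "dividing the number of individuals who met inclusion criteria, by the number who consented to participate in the trial". The next sentence adds: "Reasons why eligible individuals are not interested in participating will be recorded by the PI/recruiting therapist in the approach/screening log".

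The subsection just before it, Ability to consent, is measured by "the number of participants who provided informed consent and the number of consultee declarations".

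The table of feasibility outcomes in the data collection section has a row for each indicator. As the table reads in the available text, the Consent rate row gives the percentage "of consultee declarations", from Case Report Forms. The Ability to consent row gives the percentage "of participants consenting", from the screening and approach logs.

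For comparison, the Retention rate subsection divides those who completed a later assessment "by the number of participants who completed data collection at T1".

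**The concern.** A consent rate is the share of people who could have joined and did join. The subsection states the division the other way round, so the result moves in the wrong direction: the less willing people are to take part, the higher the reported figure. Retention, defined two subsections earlier, puts the part over the whole, so the inversion is not a convention of this article.

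The table adds a second difficulty. A percentage of consultee declarations describes the route by which participants entered. It says nothing about how many eligible people declined. Unlike a figure of 200%, it would look plausible if reported as a consent rate.

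At stake is one descriptive result under the primary feasibility aim. The Background says that recruitment, refusal and retention rates will inform the definitive trial, and the proportion who accept belongs with them.

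**Working it through.** The article states no numerical consent rate, so there is no figure to reproduce. The check concerns the direction of a ratio.

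**Inputs**
- E, the number meeting inclusion criteria: not given. Assumed here to lie between 50 and 200, for illustration only.
- C, the number consenting: 50, from Sample size ("this feasibility trial aims to recruit 50 participants in total"), and 35, which is 0.70 × 50, from Determining progression to the full trial ("70% recruitment of the intended 50 patient participants within the 13-month recruitment window").

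**Formulas**
- As written: E / C.
- Consent rate in the ordinary sense: C / E.

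The two are reciprocals. If everyone who consents also meets the criteria, then C ≤ E and E / C ≥ 1. The one exception the article allows for is a participant found ineligible after randomisation (Retention rates and withdrawal).

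| C | E (assumed) | As written, E / C | Ordinary rate, C / E |
|---|---|---|---|
| 50 | 60 | 120% | 83.3% |
| 50 | 100 | 200% | 50.0% |
| 50 | 200 | 400% | 25.0% |
| 35 | 50 | 143% | 70.0% |
| 35 | 100 | 286% | 35.0% |
| 35 | 200 | 571% | 17.5% |

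With C held fixed, the written figure rises as the ordinary rate falls.

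**The table's measure.** Suppose 10 of 50 participants entered by consultee declaration (assumed). The percentage is 10 / 50 = 20%, whether 60 or 200 people were eligible. It is neither E / C nor C / E.

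**Text against table.** The text puts consultee declarations under ability to consent and records eligible people's reasons for declining on the approach/screening log. The table puts consultee declarations under consent rate and sources them from Case Report Forms. For consent rate, text and table therefore name different quantities.

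**The denominator.** The formula counts those who met inclusion criteria, whereas the following sentence speaks of eligible individuals. These differ, because Eligibility criteria has a separate, long list of exclusions. In addition, one inclusion criterion is the ability to consent or the receipt of a consultee's assent. Read literally, a patient without capacity whose consultee declines never meets the inclusion criteria and drops out of the denominator. Turning the formula over would not settle this.

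**The case against.** The inverted sentence cannot be defended as worded, but three stronger readings are tempting and the article does not support them.

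*That a key feasibility result will be wrong.* No data collection, allocation or analysis population depends on the order of division. A rate above 100% would be noticed at the first calculation, and its reciprocal is exact from the same two counts. The sentence on eligible people's reasons for declining shows that an ordinary consent rate was meant. Other planned indicators cover nearby ground: refusals are counted under willingness to be randomised, and the table lists the shares of admissions screened and eligible, and screened and approached. This stands, and it limits the harm.

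*That the decision to proceed is affected.* The provisional progression criteria concern recruitment against target, adherence, and completion of outcome measures. Consent rate is not among them. The article says the criteria are still to be finalised, but nothing in it makes consent rate a deciding criterion.

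*That two table rows have been swapped.* This is inference. The percentage "of participants consenting" can fit ability to consent if it means participants who consented for themselves. The two adjacent cells together also reproduce the two-part measure in the text on ability to consent. The table was read by a program, and its Safety rows appear to split one phrase across two lines, so a displaced cell cannot be excluded. The table mismatch is supporting evidence only. The error in the prose does not depend on it.

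It may also be said that the statistical analysis plan will define the rate. That would answer an omission, but here a formula is stated, and stated wrongly.

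**Conclusion.** The point holds as an error of definition. The Consent rate subsection gives the reciprocal of a consent rate. Taken literally, its value is at least 100% when consenters are a subset of those meeting the criteria: 200% rather than 50% with 100 meeting criteria and 50 consenting. Those counts are assumed; the direction of the error does not depend on them.

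The table, if faithfully reproduced, assigns the indicator a different quantity, and the text is inconsistent about the denominator. These two matters would remain after the inversion is put right.

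The consequence is modest. No reported number is wrong, the correct value is recoverable from counts already planned, and the provisional progression criteria do not use it. It is a correction to make before the indicator is reported, and not a threat to the trial's conclusions.

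**What to change.** 1. In Consent rate, define the rate as the number who entered by informed consent or consultee declaration divided by the number of eligible individuals.
2. Use one denominator throughout the subsection. Say whether exclusions have been applied, and how a patient without capacity is counted when the consultee declines.
3. Under Ability to consent, report informed consents and consultee declarations, each as a share of those enrolled.
4. Check the published table and make its Consent rate cell, including the data source, match the corrected text.

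No confidence interval is needed to correct the error; that choice can be left to the statistical analysis plan.

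The cost is a few sentences and one table cell. The consents, consultee declarations and screening outcomes are already to be recorded on the logs and Case Report Forms. The one thing to confirm is that the log identifies cases where a consultee declined.
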